## Definition, assessment and causality of adverse events

An AE is any untoward medical occurrence that does not necessarily have to have a causal relationship with the investigational product. An AE can be any unfavourable, unintended clinical sign, symptom, medical complaint or clinically relevant change in laboratory variables or clinical tests. Accidents, operations not pre-planned, changes in medication or deterioration in concurrent illness are also considered as AEs.

The Investigator should rate the intensity of any AE as follows:

*Mild:* Defined as Clavien-Dindo grade I and II.

*Moderate:* Defined as Clavien-Dindo grade 3a.

*Severe:* Defined as Clavien-Dindo grade 3b-5.

The Investigator shall judge whether or not, in his/her opinion, the AE is associated with the study treatment. When stating the causality, the following nomenclature should be used:

*Unrelated:* There is little or no chance that the study treatment caused the AE.

*Possibly related:* The association of the AE with the study treatment is unknown, however, the AE is not clearly due to another condition.

*Probably related:* A reasonable temporal association exists between the AE and the study treatment. Based on the Investigator’s clinical experience, the association of the AE with the study treatment seems likely.

## Definition of serious adverse events

A serious AE is any untoward medical occurrence that at any dose:

- Results in death.
- Is life-threatening at the time of the event.
- Requires inpatient hospitalisation.
- Requires prolongation of existing hospitalisation.
- Results in persistent or significant disability/incapacity.
- Is a congenital anomaly/birth defect.

## DATA MOnitoring committee

The DMC which will include three external clinical reviewers will be responsible for making decisions on whether to move to the next dose level, as well as making decision to continue the phase III trial efficacy study after the interim safety evaluation (see interim analysis in the statistics section). The work of the DMC will be described in a DMC charter.

## Safety parameters

Clavien-Dindo morbidity was chosen as the most relevant morbidity grading system. The oxaliplatin/irinotecan/5-FU combination for systemic chemotherapy is already well known in oncology under different acronyms (FOLFIRINOX, FOLFOXIRI). As such, the toxicity profile of this triple combination is already known. This study will assess whether it is compatible with a surgical intervention using the Clavien-Dindo surgical classification. However, some basic blood chemistry as specified in section 8.3 (extended part of the HIPEC registry employed only for the dose titration study) will be added to verify the rate of non-surgical toxicity. As the 24-hour EPIC has not previously been dose-titrated, we will titrate to a maximum of 850 mg/m^2^. Clavien-Dindo 3a was excluded as a stopping factor due to its common use postoperatively after CRS+HIPEC for draining fluid collections (most commonly pleural effusion often caused by diaphragmatic stripping of the peritoneum and is dependent upon the extent of the stripping).

All patients will be reviewed at each of the dose levels by the DMC prior to advancing to the next level. It is Clavien-Dindo grade 3b-5 morbidity that will be reviewed. A dose level with ≤1/3 or ≤2/6 with 3b-4b morbidity may proceed to the next dose level. Max tolerated 3b-4b morbidity is 33 %. Statistical testing is unnecessary. All grade 5, leading to death, will halt study progression. A formal review with the DMC will ensue before the study will be allowed to continue or be terminated permanently. Two grade 5 events may be cause for study termination after DMC review.

### Interim safety analysis of the Efficacy study

After randomization, the Clavien-Dindo grade 3a-4b morbidity is expected to be approximately 25-35% when treating patients with the dose of 5-FU determined from the dose titration study. During the interim analysis of the efficacy part of the trial, the DMC will use the morbidity rate of the standard arm and compare it to the experimental arm. If all Clavien-Dindo grade 3-4 complications resolve in-hospital and occur at a maximum rate of 40%, the trial will pass the interim review. If complications lead to permanent sequelae or the rate is higher than 40% a detailed review by the safety committee will ensue prior to letting the efficacy study continue. Comparison with the standard arm will assist in determining the risk/possible benefit ratio. In particular, if the mortality rate is increased, it will be grounds for discontinuing the trial. The trial may be allowed to continue despite increased morbidity if the mortality rates are the same and if the morbidity is of a temporary nature, not leading to permanent functional loss. The decision will be made by the DMC. If necessary, dose reduction may be considered in order to continue and complete the efficacy study.

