### Efficacy study

Figure 2: Flowchart for the efficacy study

| All colorectal cancers with peritoneal metastases | | | | |
| --- | --- | --- | --- | --- |
| ↓  Randomization intraoperatively  ↙ ↘ | | | | |
| **A: Standard HIPEC**  **(70 patients)**   1. Oxaliplatin  - 460 mg/m^2^ (HIPEC)  1. 5-fluorouracil  - 400 mg/m^2^ IV bolus (Intraop)  1. Calcium folinate  - 60 mg/m^2^ IV (Intraop) | |  | **B:** **Intensified HIPEC+EPIC**  **(70 patients)**   1. Oxaliplatin    - 360 mg/m^2^ (HIPEC) 2. Irinotecan    - 360 mg/m^2^ (HIPEC) 3. 5-FU Bolus    - 400 mg/m^2^ IV (Intraop) 4. Calcium folinate 5. 60 mg/m^2^ IV (Intraop) 6. 5-FU 24-hr EPIC  - According to the dose titration study | |
|  | |  | Prophylactic G-CSF postop day 4-8 | |
| ↓ |  | | | ↓ |
| Interim safety evaluation:  Grade 3-5 Clavien-Dindo morbidity comparison | | | | |
| ↓ | | | | |
| **A: Standard HIPEC**  **(163 patients)** | |  | **B:** **Intensified HIPEC+EPIC**  **(163 patients)** | |
| ↓ | |  | ↓ | |
| Primary endpoint:   - 12-month RFS   Secondary endpoints:   - Overall survival and RFS up to 5 years: Through the HIPEC registry - QoL: Through the QoL registry - Morbidity: Through the HIPEC registry | | | | |

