#### Interim analysis

The Clavien-Dindo grade 3-4 morbidity is expected to be approximately 0.35 (35%) for patients receiving the maximum dose of 5-FU. Allowing for a small increase in morbidity to 0.40 and an accepted 95% confidence interval width of 0.15, at least 66 patients are needed in the experimental arm to determine whether the arm deviates from the expected morbidity rate. The total sample size will be 140 (70 per arm) for an interim trial safety evaluation (circa 50% of trial included). If the Clavien-Dindo grade 3-4 morbidity falls outside of the 40% mark, then a Fisher’s exact test comparison between the standard and experimental arm will be performed together with a mortality comparison. Concerning in-hospital mortality, a maximum rate of 5% will be set. This planned interim safety evaluation will be unpublished. If the morbidity is increased beyond the set mortality limit or the increase is of a more serious nature, the trial will either be discontinued or alternatively, depending on the character of the complications, a lower dose level may be employed.

The overall survival and recurrence free survival will be reviewed during this interim safety evaluation to see if a primary endpoint of overall survival is attainable with increased cohort size instead of 12-month RFS. If attainable depending on inclusion rate, the endpoint will be changed, and a new sample size calculation will be performed. Likewise, a choice between 3 or 5 year follow-up will be made. Alternatively, trial futility will be determined if no differences at all are forthcoming even in the RFS setting. In this case, the trial will close prematurely. A decision to close the trial is made by the sponsor in conjunction with site investigators.

Possible changes of dose level, endpoint, sample size calculation or other substantial changes will be submitted to the MPA and ERA as an amendment to the protocol.

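### The protocol's interim safety passages disagree on whether the look is comparative: the pass rule uses only an absolute 40% rate, and the between-arm test is run only once that rate is exceeded.

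*Protocol*

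**What the plan says.** The interim safety look after 140 randomised patients (70 per arm) is described in four places in the Protocol.

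- **Section 8.2.2, Figure 2.** The look is labelled "Grade 3-5 Clavien-Dindo morbidity comparison".
- **Section 12.5.1.** For patients treated at the 5-FU dose taken from titration, "the Clavien-Dindo grade 3a-4b morbidity is expected to be approximately 25-35" percent. It then says that "the DMC will use the morbidity rate of the standard arm and compare it to the experimental arm", with no condition attached. The next sentence is the pass rule: "If all Clavien-Dindo grade 3-4 complications resolve in-hospital and occur at a maximum rate of 40%, the trial will pass the interim review". Above 40%, or with permanent sequelae, a detailed review follows in which the standard arm is consulted.
- **Section 13.2.1, Interim analysis.** The trigger for the formal test is "If the Clavien-Dindo grade 3-4 morbidity falls outside of the 40% mark"; only then is a Fisher's exact "comparison between the standard and experimental arm will be performed together with a mortality comparison".
- **Synopsis, Criteria for evaluation.** The study continues if the experimental arm's 95% CI lies at or below 0.4, for grades 3-5.

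On grade 3a, section 12.5 says, for dose titration, that "Clavien-Dindo 3a was excluded as a stopping factor due to its common use postoperatively after CRS+HIPEC for draining fluid collections", naming as the cause "most commonly pleural effusion often caused by diaphragmatic stripping of the peritoneum".

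**The concern.** Section 5.4 says this look was added in place of a phase II trial, and section 12.1 limits formal DMC safety review in phase III to it unless unexpected serious events arise. It is therefore the main planned check on the toxicity of the three-drug regimen.

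Both randomised arms have the same operation, so the control arm is what separates the effect of the added drugs from the surgical background. Figure 2 and one sentence of 12.5.1 use it. The pass sentence does not, and 13.2.1 requires the test only on the failing side. A DMC following the pass sentence could clear an experimental-arm rate well above control without any specified between-arm analysis. A DMC following the synopsis would apply a much stricter rule to the same data. The grades counted also differ: 3-4 in the pass sentence and 13.2.1, 3-5 in the synopsis and Figure 2.

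Grade 3a adds to this. The protocol itself describes it as common and often surgical. A rule that counts it without reference to the control arm says less about drug toxicity than one that uses both arms.

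**Working it through.** **Inputs from the Protocol.** 70 per arm and an expected experimental-arm rate of 0.35 (13.2.1); limit 0.40 (12.5.1, 13.2.1); CI version (synopsis); significance level 0.05 (13.4).

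**Assumptions.** Two-sided Fisher test. The 40% limit applies to the experimental arm; the pass sentence does not name the arm, but 13.2.1 sizes the look for that arm. Control-arm rates of 15%, 20% and 25% are illustrative, because the documents state none.

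**The plan's own figure.** Section 13.2.1 says at least 66 experimental patients are needed for a 95% CI width of 0.15. With n = 1.96² p(1−p)/h²:
- h = 0.15 gives 39 (p = 0.35) or 41 (p = 0.40);
- h = 0.075 gives 156 or 164.

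Neither gives 66. This is a separate matter and does not affect what follows, which uses the planned 70.

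**Step 1. Point-rate rule.** 0.40 × 70 = 28, so 28 or fewer events pass. With X ~ Bin(70, p), P(X ≤ 28) is 0.998, 0.84, 0.55 and 0.24 at true experimental rates of 25%, 35%, 40% and 45%. The control rate does not enter.

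**Step 2. A just-passing result.** Experimental 28/70 (40.0%):

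| Control | Difference | Wald 95% CI | Fisher p |
|---|---|---|---|
| 16/70 (22.9%) | 17.1 points | 2.0 to 32.3 | 0.045 |
| 17/70 (24.3%) | 15.7 points | 0.5 to 31.0 | 0.07 |

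The half-width is 1.96 × √(0.400 × 0.600/70 + 0.229 × 0.771/70) = 0.151 in the first row. Both results pass, and 13.2.1 requires no test for either. Fisher's p stays below 0.05 for any control count of 16 or fewer.

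**Step 3. How often the rule passes when the test would have been significant.** Sum Bin(a; 70, p_C) × Bin(b; 70, p_E) over all control counts a and experimental counts b with b ≤ 28, b > a and Fisher p < 0.05:

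| Assumed control / experimental | P(pass) | Power of an unconditional Fisher test | P(pass and Fisher significant) |
|---|---|---|---|
| 25% / 35% | 0.84 | 0.20 | 0.10 |
| 20% / 35% | 0.84 | 0.44 | 0.30 |
| 15% / 35% | 0.84 | 0.73 | 0.57 |

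**Step 4. Synopsis rule.** The largest count whose upper 95% limit is at most 0.40:
- Wald: 20/70 (upper limit 0.392);
- Wilson: 19/70 (0.385; 20/70 gives 0.4005);
- Clopper-Pearson: 19/70 (0.391).

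So at most 19 or 20 of 70 (27% to 29%) passes. At the protocol's expected 35%, the chance of passing is 0.10 (19/70) or 0.16 (20/70), against 0.84 under the point-rate rule.

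**The case against.** A reader might infer that the interim look cannot separate drug toxicity from surgical background at all. The documents do not support that. Section 12.5.1 tells the DMC, without condition, to compare the arms, and Figure 2 agrees. Only the Fisher test is conditional. What remains is that this comparison has no measure, margin or stated role when the rate is 40% or below.

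A reader might also infer that a heavy surgical case mix would wrongly stop the trial. If both arms were truly at 45%, the limit would be exceeded with probability 0.76, but the consequence is a detailed review with the standard arm, plus Fisher's test and a mortality comparison. That side already uses the control arm.

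It is tempting to read 25-35% as the surgical background. Section 12.5.1 gives it for patients treated at the titrated 5-FU dose, so it is an expectation for the experimental regimen. Passing 84% of the time at 35% is therefore not a fault in itself.

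Counting grade 3a in phase III does not contradict section 12.5. That exclusion concerns small uncontrolled titration cohorts, it says only that the cause is most commonly or often surgical, and randomisation balances such events on average.

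Other protections exist: the condition that events resolve in-hospital, review of permanent sequelae, the 5% in-hospital mortality limit, referral of serious events to the DMC, and early review at any site investigator's request. The DMC charter, which is not shown, may say more. These points narrow the concern, but none of them specifies how a temporary excess over control that stays at or below 40% is to be assessed.

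**Conclusion.** The point holds as an inconsistency with a practical gap on the passing side. The Protocol describes the look as comparative in two places, as a single-arm point rate in the pass sentence, and as a single-arm CI in the synopsis; section 13.2.1 requires the between-arm test only above 40%. The versions differ materially: 28/70 passes under one, while at most 19 or 20 of 70 passes under another.

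Under the point-rate version, an excess that Fisher's test would call significant can pass with no test required, with probability of about 10% to 57% over the assumed control rates of 25% down to 15% and an experimental rate of 35%. Those control rates are assumptions, and the share of grade 3a events is not given either. The gap concerns what the DMC is shown and how it is used. It does not show that the 40% limit is wrong.

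**What to change.** 1. Reconcile the synopsis, Figure 2, section 12.5.1 and section 13.2.1 on the grades counted, on point rate versus CI, and on the role of the control arm.
2. In section 13.2.1, delete the condition that makes the between-arm comparison depend on exceeding 40%.
3. At the interim, always give the DMC both arms' rates of grade 3-5 and, separately, of grade 3b-5 (the dose-titration endpoint), each with the risk difference and its 95% CI.
4. Have the sponsor and the DMC state, in 12.5.1 and the charter, what role that comparison plays when the rate is 40% or below.

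The cost is wording in these sections and the charter, plus one table by grade and arm from morbidity data already collected. The drawback is imprecision: at 70 per arm the 95% CI for the difference is about ±15 points, and an unconditional Fisher test has power of only 0.20 at 25%/35% and 0.44 at 20%/35%. The estimate therefore informs DMC judgement and is not a sharp test. No threshold or continuation rule is proposed; those remain with the sponsor and the DMC.

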## Reporting of adverse events, serious adverse events, AND suspected unexpected serious adverse reactions

All adverse events will be reported in a separate eCRF adverse event report section of the HIPEC registry created for this trial. It is the responsibility of the site investigator or co-investigator to fill out an eCRF Adverse Event form in the HIPEC registry. All investigators have access through their SITHS ID cards to the registry. One form per AE is to be filled out. It may be filled out as part of the postop follow-up at predetermined time points of follow-up, but it may be filled out in between these time points since the patients are admitted to the hospital and under daily surveillance during 10-14 days. If classified as SAE it needs to be filled out within 24 hrs from being informed about the event.

Serious adverse events with a possible or probable relationship to the study medication including events leading to a deadly outcome need to be brought to the attention of the DMC. The adverse event eCRF section of the HIPEC registry will include a list box if an adverse event needs to be brought to the DMC for review. An automated email will be sent to the coordinating investigator (who is also the sponsor representative) who will be responsible for discussing the event with the DMC.

The Investigator’s initial report of serious AEs should as far as possible be supplemented by detailed information on diagnosis/symptoms, the relationship with the start of treatment and any further relevant data in the eCRF section.

If the SAE is assessed as unexpected and possibly/probably related to the IMP, i.e. a Suspected, Unexpected Serious Adverse Reaction (SUSAR) that are fatal or life-threatening, it shall be reported to the Medical Products Agency (MPA) as soon as possible and at the latest within 7 calendar days from the first knowledge by the Sponsor. The report shall as far as possible be supplemented by additional information, but at the latest within a further 8 calendar days. It is the responsibility of the Sponsor to report SUSARs to the MPA. It will be reported on CIOMS forms by e-mail to be registered in the EudraVigilance database by MPA.

The reporting of other SUSARs to the MPA shall be done as soon as possible, but not later than 15 calendar days after the first knowledge by the sponsor.

## Follow-up of adverse events and serious adverse events

All patients are followed up within 3 months postoperatively within normal clinical routine to evaluate the potential long-term effects of previous adverse events. If an AE is not recovered after 3 months, it will be followed up until recovered or stabilized.

## ANNUAL Development safety update report (DSUR)

As long as the study is ongoing, the Sponsor will annually send a summary of all SAEs to the MPA. The report will also summarize the safety and the risk for the subjects in the trial. The report will contain an updated risk/benefit summary.

# STATISTICS AND DATA MANAGEMENT

## Data management

The patient is registered preoperatively in the HIPEC registry during the preoperative visit at the surgical outpatient clinic. This is the time that informed consent is made. If the patient opts to join the trial, there is a check box for the phase I dose titration study, which will change to phase III efficacy study after phase I is complete in the HIPEC registry. Once included, the HIPEC registry will automatically set reminders to site investigators when data needs to be put into the registry. Clinical registries are very good sources for researchers, however, the timing of data input is sometimes late, thus automatized reminders will be used to keep the registry constantly up-to-date during this trial.

Data input will be reviewed by the monitors. Incomplete data, as found by the monitors, will be listed in a data clarification form to be sent to respective site to resolve inconsistencies and missing information. A copy will be returned to the sponsor.

The HIPEC registry includes a number of variables that are not considered important for monitoring. The following variables are defined as monitoring points:

1. Study registration and diagnosis

(the study registration visit charting – study ID number, inclusion criteria, and diagnosis)

1. HIPEC/EPIC Treatment administered
2. Adverse events
3. Blood chemistry toxicity and medications
4. 12-month RFS as defined by the radiologist report

As part of informed consent, the patients will allow monitoring through the NPÖ (Nationella Patient Översikten) so that access to source data is made possible. The medical charting through the NPÖ is defined as the source data for all monitored variables.

## Statistical analysis

### Statistical methods

#### Dose titration study

The dose titration study will include 3 patients at each dose level, with a possibility to include 3 more patients if more than 1 patient experiences morbidity grade 3b-5 (3 + 3 design). In order to complete all 5 dose levels 15-30 patients will be needed depending on how often the second three patients are needed at each dose level. The toxicity follow-up is 30 days if no incidents occur. If the postoperative rehabilitation is slower or an incident occurs, the follow-up period may be extended by the site Principal Investigator or Co-investigator. Circa 3-4 colorectal cancer patients are treated with CRS+HIPEC each week in Sweden. Dose titration can be completed within 15-30 weeks.

#### Interim analysis

The Clavien-Dindo grade 3-4 morbidity is expected to be approximately 0.35 (35%) for patients receiving the maximum dose of 5-FU. Allowing for a small increase in morbidity to 0.40 and an accepted 95% confidence interval width of 0.15, at least 66 patients are needed in the experimental arm to determine whether the arm deviates from the expected morbidity rate. The total sample size will be 140 (70 per arm) for an interim trial safety evaluation (circa 50% of trial included). If the Clavien-Dindo grade 3-4 morbidity falls outside of the 40% mark, then a Fisher’s exact test comparison between the standard and experimental arm will be performed together with a mortality comparison. Concerning in-hospital mortality, a maximum rate of 5% will be set. This planned interim safety evaluation will be unpublished. If the morbidity is increased beyond the set mortality limit or the increase is of a more serious nature, the trial will either be discontinued or alternatively, depending on the character of the complications, a lower dose level may be employed.

The overall survival and recurrence free survival will be reviewed during this interim safety evaluation to see if a primary endpoint of overall survival is attainable with increased cohort size instead of 12-month RFS. If attainable depending on inclusion rate, the endpoint will be changed, and a new sample size calculation will be performed. Likewise, a choice between 3 or 5 year follow-up will be made. Alternatively, trial futility will be determined if no differences at all are forthcoming even in the RFS setting. In this case, the trial will close prematurely. A decision to close the trial is made by the sponsor in conjunction with site investigators.

Possible changes of dose level, endpoint, sample size calculation or other substantial changes will be submitted to the MPA and ERA as an amendment to the protocol.

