| Criteria for evaluation:  Safety: Safety will be assessed by the Clavien-Dindo classification and reporting of Adverse Events.  The maximum tolerated dose of 5-FU will be determined by giving the first 15-30 patients escalating doses of 5-FU. The morbidity of each dose level of 5-FU 24-hour EPIC will be evaluated by the Data Monitoring Committee 30 days post-treatment. A dose level with ≤1/3 or ≤2/6 with 3b-4 Clavien-Dindo morbidity may proceed to the next dose level. Following the dose titration study, all patients will receive the maximum dose of 5-FU. An interim safety evaluation will be performed after the first 140 patients have been randomized and treated with HIPEC or HIPEC in combination with EPIC. The Clavien-Dindo grade 3-5 morbidity is expected to be approximately 0.35 (35%). If the experimental arm’s 95% CI falls within 0.4 or below, the study will be allowed to continue.  Efficacy: Recurrence free survival (RFS) is determined at 12-months post treatment through the HIPEC registry. Postoperative complications rates with-in 30 days, 5-year overall survival and RFS are further determined through the HIPEC registry and quality of life is assessed by questionnaires through the QoL registry. | | |
| **Dosage of Investigational Products:**  The maximum tolerated dose (MTD) of 5-FU will be determined by giving the first 15-30 patients escalating doses of 5-FU. The morbidity of each dose level of 5-FU 24-hour EPIC will be evaluated by the Data Monitoring Committee within 30 days post-treatment. A dose level with ≤1 of 3 patients or ≤2of 6 patients (extended group size) with 3b-5 morbidity may proceed to the next dose level. If the frequency of 3b-5 morbidity is higher, MTD has been passed and the dose of 5-FU in the efficacy study will be the next lower dose level. If MTD is not reached the highest dose level of 5-FU (850 mg/m^2^) will be used. | | |
| Statistical methods:  Recurrence free and overall survival of the two arms will be compared using the parameters: treatment arm, age, PCI, CC score, use of systemic perioperative chemotherapy (neoadjuvant and/or adjuvant), concomitant liver metastases resection, colon or rectal primary tumor, and lymph-node metastasized primary tumor.  QoL will be analyzed by comparing the answers to questions 29 and 30 in QLQ-C30 by Mann-Whitney U test and Freidman’s repeated measures ANOVA test. Specifically, differences between the sexes will be investigated.  Statistical significance will be set at p=0.05. | | |

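### The interim safety sizing does not follow from its own inputs (66 patients do not give a 95% interval 0.15 wide), and the synopsis states a different continuation condition from sections 12.5.1 and 13.2.1

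*Protocol*

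**What the plan says.** **Sizing (Protocol 13.2.1, Interim analysis).** The expected rate is given as "The Clavien-Dindo grade 3-4 morbidity is expected to be approximately 0.35 (35%) for patients receiving the maximum dose of 5-FU". The text continues "Allowing for a small increase in morbidity to 0.40", and for "an accepted 95% confidence interval width of 0.15, at least 66 patients are needed in the experimental arm". The interim is then set at 140 patients, 70 per arm.

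**Decision condition and event, by section.**

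| Place | Event | Condition | If not met |
|---|---|---|---|
| Synopsis, Criteria for evaluation | Grade 3-5, expected about 35% | "95% CI falls within 0.4 or below, the study will be allowed to continue" (experimental arm) | Not stated |
| 8.2.2, Figure 2 | "Grade 3-5 Clavien-Dindo morbidity comparison" | None given | None given |
| 12.5.1 | Grade 3a-4b for the expected rate, grade 3-4 for the condition | All such complications resolve in hospital and "occur at a maximum rate of 40%, the trial will pass the interim review" | Detailed review; the DMC decides |
| 13.2.1 | Grade 3-4, expected 35% | Rate not beyond the 40% mark | Fisher's exact test between arms plus a mortality comparison |

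Section 12.5.1 gives the expectation as a range: "the Clavien-Dindo grade 3a-4b morbidity is expected to be approximately 25-35" per cent.

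**The concern.** There are two faults. First, the precision that justifies the interim size is not what that size delivers. A DMC member reading 13.2.1 would expect an interval 0.15 wide and would receive one about half as wide again. Second, the synopsis judges an interval for grade 3-5 events, while the body judges a rate of grade 3-4 events. An interval criterion and a rate criterion set at the same 40% are very different hurdles with 70 patients.

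Section 5.4 says this interim analysis was added in place of a phase II trial. Section 12.1 makes it the only scheduled formal DMC safety review of the efficacy study, unless unexpected serious events prompt an earlier one. The DMC therefore needs a single condition to apply and a true statement of how precise its estimate will be.

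**Working it through.** **Inputs.** Expected rate p = 0.35, allowed rate 0.40, 95% confidence, width 0.15, stated n = 66, planned n = 70 per arm (all 13.2.1). Range 0.25 to 0.35 (12.5.1).

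**1. Trying to reproduce 66.** For an interval of half-width d around one proportion, n = 1.96² p(1−p)/d².

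- Full width 0.15 (d = 0.075): at 0.35, 3.8415 × 0.2275/0.005625 = 155.4, so 156. At 0.40, 3.8415 × 0.24/0.005625 = 163.9, so 164. That is about the whole planned arm of 163.
- Half-width 0.15: at 0.35, 38.8, so 39. At 0.40, 41.0, so 41.
- Wilson, Agresti-Coull, Jeffreys and Clopper-Pearson intervals need 152-166 (at 0.35) and 161-175 (at 0.40) for full width 0.15, and 36-45 for half-width 0.15.
- A one-sided 95% bound at distance 0.15 needs 28-29.

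None of these gives 66. Numbers near 66 appear only when the stated inputs are replaced:

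- an 80% interval of full width 0.15 at 0.35: 1.2816² × 0.2275/0.005625 = 66.4;
- a one-sided 5% one-sample test with 80% power for 0.40 against 0.55 (66.6), or for 0.35 against 0.50 (64.6).

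The protocol states none of these.

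**2. Precision actually obtained.** Width = 2 × 1.96 × √(p(1−p)/n).

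- n = 66: 0.230 at 0.35 and 0.236 at 0.40.
- n = 70: 0.223 at 0.35 and 0.230 at 0.40, i.e. about ±0.11 to ±0.115.

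**3. The two conditions with 70 patients.** Read the synopsis as requiring an upper 95% limit of at most 0.40.

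- 19/70: upper limit 0.376 (Wald), 0.385 (Wilson), 0.391 (Clopper-Pearson). Met by all three.
- 20/70: 0.392 (Wald), 0.4005 (Wilson), 0.406 (Clopper-Pearson). Met by Wald only.
- 21/70: 0.407 (Wald). Not met.

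So the synopsis condition allows at most 19 events (20 with Wald limits). An observed rate of at most 40% allows 28, since 0.40 × 70 = 28. Exact binomial probabilities:

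| True rate | Synopsis condition missed (Wald to exact/Wilson) | Rate ≤ 40% met |
|---|---|---|
| 25% | 20% to 29% | 99.8% |
| 30% | 55% to 65% | 97% |
| 35% | 84% to 90% | 84% |
| 40% | 97% to 98% | 55% |
| 45% | more than 99% | 24% |

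The last column covers only the rate part of 12.5.1. Because that section also requires in-hospital resolution, these figures are upper bounds for meeting its full condition.

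**4. Where the sections part.** Counts of 20 to 28 (21 to 28 with Wald limits) miss the synopsis condition but meet the 40% rate. At a true 35% the chance of such a count is 0.842 − 0.104 = 0.74 (0.842 − 0.158 = 0.68 with Wald). This treats the event as the same in both places. Counting grade 5 in one and not in the other adds a further difference that the protocol gives no figures to size.

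**The case against.** A reader might infer that the synopsis rule would fail the trial about nine times in ten at the expected morbidity. The protocol does not support that. The synopsis says when the study may continue and is silent on a miss. Section 12.5.1 sends a rate above 40% to detailed review and allows continuation despite raised morbidity, and 13.2.1 sends it to a between-arm test. Missing the condition is a trigger for judgement by the DMC. The 90% also belongs to exact or Wilson limits at 35%. It is 84% with Wald limits and far lower at the bottom of the 12.5.1 range.

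The reading of the synopsis matters too. If its wording meant only that the interval must include or lie below 0.40, up to 36/70 would satisfy it. That is met over 99% of the time at 35%, but also 64% of the time at a true 50%. The upper-limit reading is the natural one, but the text should not leave a choice.

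Sections 12.5.1 and 13.2.1 are largely compatible: both use grade 3-4, both use 40%, and both lead to a comparison with the standard arm. The conflict is mainly between the synopsis and the body, with Figure 2 siding with the synopsis on the event. Nor are deaths unmonitored where grade 5 is left out of the morbidity rate: 13.2.1 sets a 5% ceiling on in-hospital mortality, and 12.5.1 makes increased mortality grounds for discontinuing.

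Finally, 66 may come from a mislabelled test calculation, since 13.2.1 speaks of determining whether the arm deviates from expectation. That could explain the number but does not make the stated interval basis correct. A DMC charter is planned (12.4), but it cannot follow protocol sections that disagree.

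**Conclusion.** The point holds as a wrong stated figure plus a contradiction between sections. The number 66 does not follow from a 95% interval of width 0.15 under a full-width, half-width or one-sided reading, and the precision available with 70 patients is about 0.22 to 0.23. The synopsis and the body use different decision statistics and different events. At the protocol's own 35%, roughly 70% of possible outcomes (68-74%) would be routed differently by the two.

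This rests on the upper-limit reading of the synopsis, on reading the 40% mark in 13.2.1 as an observed rate, and on 70 evaluable patients in the experimental arm. The sizing error depends on none of these. Whether 40% is the right clinical limit is not judged here.

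**What to change.** - **13.2.1:** delete the 0.15/66 justification and state what 70 per arm gives, a 95% interval about 0.22 to 0.23 wide (±0.11 to ±0.115) at rates of 35-40%.
- **Synopsis, Figure 2, 12.5.1 and 13.2.1:** reconcile to one event definition (with or without grade 5), one expected rate and one decision statistic, chosen by the sponsor with the DMC. State what follows when the condition is not met, and align the DMC charter.
- **Optional:** print the probability of meeting the chosen condition at a few true rates.

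The cost is protocol wording and charter alignment. The interim size stays at 140. The stated precision becomes less favourable.
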